#### Predictor, Moderator, and Mediator Analyses

Predictors and moderators of changes in SIP will be analyzed on an exploratory basis. They will include, e.g., lifelong and acquired GPPPD, experiences of sexual abuse, and symptom severity. Fear of sexuality, penetration-related cognitions and exercise intensity will be examined as mediators of changes in SIP *via* structural equation modeling. Separate moderator analyses will be conducted using the PROCESS macro for SPSS. The analyses will include the main effect of the baseline variable, the main effect of the treatment condition (IG and WCG), and the interaction of the baseline variable and the treatment condition. To assess relevant subgroup effects, follow-up simple slope analyses for possible significant interaction effects will be conducted. Therefore, the slope and the significance of the intervention main effect will be evaluated for conditional values (one SD below and one SD above the mean) of the moderator.

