## Background

Genito-pelvic pain/penetration disorder (GPPPD) is a new diagnosis included in the 5th edition of the Diagnostic and Statistical Manual of Mental Disorders (DSM-5), which merged the revised definitions of both female sexual dysfunctions dyspareunia and vaginismus (1). At least one of the following persistent or recurrent criteria characterizes GPPPD: (1) difficulties with vaginal penetration during intercourse, (2) genito-pelvic pain during vaginal intercourse or penetration attempts, (3) fear or anxiety associated with genito-pelvic pain or vaginal penetration, or (4) tightness of the pelvic floor muscles during attempted vaginal penetration (1). One or more of these symptoms have to be present for at least 6 months and must cause clinically significant distress. GPPPD can be classified as either lifelong or acquired and, depending on the level of distress as mild, moderate or severe (1). The fusion of vaginismus and dyspareunia under a new classification and set of criteria was due to the significant overlap in clinical presentation, and exceeding difficulties to distinguish between the two reliably (2, 3).

The prevalence of GPPPD has not been ascertained due to the novel criteria set. Reported prevalence rates in the general population vary between 3 and 25% for dyspareunia (4–8) and 0.4 and 6.6% for vaginismus (6, 7, 9). Prevalence estimates are heterogeneous due to, e.g., varying diagnostic criteria, assessment methods, study design, and sample characteristics (10–12).

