### Strengths

This study will contribute significantly to the literature and empirically tested treatments for GPPPD because, to the best of our knowledge, it is the first to investigate the efficacy of a guided Internet-based intervention for the treatment of GPPPD. A major strength of this study is its robust RCT design, commonly regarded as the gold standard for clinical trials. We will also include a high number of participants in this study to ensure sufficient power. In addition, missing data will be handled with MIs, and statistical analyses will be conducted with state-of-the-art methods. Another major advantage of this study is that it also includes a questionnaire on male sexual dysfunction, which the partners of participants will complete. The inclusion of this questionnaire will allow for an analysis of the influence of partners’ sexual disorders on participants’ treatment progress. Moreover, little is known about other moderators and mediators of the treatment outcome for GPPPD. In this study, potential moderators and mediators will be analyzed to understand for which women Internet-based interventions are likely to be the most effective and under what circumstances the intervention can be optimized for participants based on personal characteristics.

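### Probing interactions at one SD below and above the mean does not give subgroup effects for the binary lifelong/acquired classification

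*Protocol article*

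**What the plan says.** The section Predictor, Moderator, and Mediator Analyses gives examples of the baseline variables to be studied: "lifelong and acquired GPPPD, experiences of sexual abuse, and symptom severity". The moderator model contains the baseline variable, the treatment condition and "the interaction of the baseline variable and the treatment condition". If the interaction is significant, "follow-up simple slope analyses for possible significant interaction effects will be conducted". The purpose is given as "To assess relevant subgroup effects", and the slope and significance of the intervention effect are to be evaluated at "conditional values (one SD below and one SD above the mean) of the moderator". The section has no separate rule for variables with two categories.

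The Background describes the first listed variable as an either/or classification: "GPPPD can be classified as either lifelong or acquired". Under Strengths, the moderator and mediator work is meant "to understand for which women Internet-based interventions are likely to be the most effective".

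**The concern.** One SD either side of the mean is a conventional way to describe low and high values of a continuous score. A two-category variable has no low and high values in that sense, only two codes. Its mean is a proportion, and one SD either side of a proportion generally does not land on either code. Applied literally to lifelong versus acquired GPPPD, the rule evaluates the intervention effect at two values that no woman has.

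What is at stake is the reported subgroup result. If the two slopes are read as the effects in acquired and in lifelong GPPPD, as the stated purpose invites, both estimates and both significance statements describe something else. The article wants these analyses to show which women benefit most, and this output would not answer that for this variable.

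**Working it through.** **Inputs.** From the moderator section: the two probe points, the model (baseline variable, treatment, interaction) and the list of variables. From the Background: lifelong/acquired has two categories. From Sample Size Calculation: N = 200, used only for the small-sample SD below. The article gives neither the share of women with lifelong GPPPD nor any expected subgroup effects, so both are assumptions here. It also gives no figure of its own on this point that could be reproduced.

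**Step 1: where the points fall.** Code acquired = 0 and lifelong = 1, with share p coded 1. The mean is p and the SD is sqrt(p(1−p)), so the points are p − sqrt(p(1−p)) and p + sqrt(p(1−p)).

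- The lower point exceeds 0 when p > sqrt(p(1−p)), that is, when p > 1 − p, so p > 0.5.
- The upper point exceeds 1 when sqrt(p(1−p)) > 1 − p, which again means p > 0.5.
- For p < 0.5 the picture is mirrored: the lower point falls below 0 and the upper point lies between 0 and 1.

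So at any split other than 50/50, one point lies strictly between the codes and the other lies outside them.

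**Step 2: numbers for assumed shares.** The distance between the points is 2·sqrt(p(1−p)). The true distance between the categories is 1.

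| Assumed share p | SD | Lower point | Upper point | Distance |
|---|---|---|---|---|
| 0.5 | 0.500 | 0.00 | 1.00 | 1.00 |
| 0.6 | 0.490 | 0.11 | 1.09 | 0.98 |
| 0.7 | 0.458 | 0.24 | 1.16 | 0.92 |
| 0.8 | 0.400 | 0.40 | 1.20 | 0.80 |
| 0.9 | 0.300 | 0.60 | 1.20 | 0.60 |

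The difference between the two reported slopes is the interaction coefficient times the distance. It is therefore smaller than the true group difference by about 2%, 8%, 20% and 40% at shares of 0.6, 0.7, 0.8 and 0.9. Using the sample SD at N = 200 changes almost nothing: at p = 0.5 the points become −0.001 and 1.001.

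**Step 3: what would be reported.** Assume intervention effects on the log-odds scale of 0.2 in acquired and 1.2 in lifelong GPPPD, so the interaction coefficient is 1.0, with p = 0.8.

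- Lower point: 0.2 + 0.40 × 1.0 = 0.60, odds ratio exp(0.60) = 1.82. The acquired group's own value is exp(0.2) = 1.22.
- Upper point: 0.2 + 1.20 × 1.0 = 1.40, odds ratio exp(1.40) = 4.06. The lifelong group's own value is exp(1.2) = 3.32.

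The lower figure is a weighted blend: 0.6 × 0.2 + 0.4 × 1.2 = 0.60. The upper figure is an extrapolation beyond the lifelong group. In this example the smaller (acquired) group is misstated more, by 0.40 against 0.20 on the log-odds scale.

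**Step 4: what does not change.** The interaction coefficient and its test do not depend on the probe points. The effect in the group coded 0 is the treatment coefficient, and the effect in the group coded 1 is that coefficient plus the interaction. Both come from the same fit.

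**The case against.** The other side has several fair points.

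- **Scope.** The article never says that the rule covers every moderator. It is one parenthetical in a condensed report, the variable list is introduced as examples, and it covers predictors and moderators jointly. Lifelong/acquired is therefore not separately assigned to the moderator analysis. This stands as a limit on the wording. Still, the rule is written without exception, and using the variable as a moderator is the natural reading of a list that covers both roles. What is criticised is a stated rule that does not fit a named variable, not a detail left out.
- **Fit elsewhere.** The moderator singled out in the Aims, partner sexual dysfunction, is measured with a scored questionnaire, for which ±1 SD is conventional. Symptom severity may suit the rule too. This stands.
- **Validity.** Estimates at 0.40 and 1.20 are valid for those values. They mislead only when read as group effects. This is correct, but subgroup effects are what the slopes are for.
- **Reach.** Harm requires a categorical moderator, a significant interaction and literal use of the rule, all within exploratory work. This stands and keeps the matter small. An analyst may well probe the two categories anyway, but that would depart from the written rule.

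A reader might extend the criticism to the sexual abuse measure and suppose that its mean minus one SD falls below the scale minimum. The article gives no distribution, prevalence or cut-off for that measure in this sample, so the documents do not establish this. A reader might also infer that the moderation test itself is wrong; Step 4 shows that it is not.

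**Conclusion.** The point holds in a limited form. Followed as written, the rule does not deliver subgroup effects for lifelong versus acquired GPPPD unless the sample splits exactly 50/50. The size depends on a share that the article does not give: the contrast between slopes is about 2% too small at 60/40, 20% at 80/20 and 40% at 90/10. The odds ratios in the example rest further on assumed effects. The conclusion also assumes that lifelong/acquired is used as a moderator and that the rule is applied literally.

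The primary chi-square test, the sample size and the interaction tests are untouched. This is a minor correction to an exploratory analysis.

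**What to change.** Add one sentence to the moderator section: for categorical moderators, the intervention effect with its 95% confidence interval is reported in each observed category, and the points one SD below and above the mean are used for continuous moderators only.

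This needs no new data, no additional model and no change to the primary analysis, because the category effects come from the model already planned.

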## Discussion

Genito-pelvic pain/penetration disorder is a major strain on afflicted women and their partners and adversely affects sexual satisfaction, sexual functioning, physiological, and psychological well-being. One study showed that treatment involving exposure and face-to-face guidance by a therapist can be an effective means to treat lifelong vaginismus (105). This kind of treatment is, however, very resource-intensive, and access is also limited. Thus, Internet-based guided self-help interventions drawing on the principles of multimodal cognitive-behavioral therapy could be an effective first step in stepped treatments of GPPPD because they are likely to lower the threshold of treatment utilization due to higher levels of anonymity. As a result, women reluctant or unable to participate in face-to-face interventions would be able to seek treatment. Internet-based interventions would also be an option for women at an early stage or with less severe symptoms of the disorder, thus perhaps preventing a chronic course of GPPPD.

Throughout the treatment, participants are supported by an eCoach as guidance, such as that provided in this study, has been shown to increase adherence rates when it comes to Internet-based interventions (106). To increase treatment adherence, eCoaches will send participants feedback on completed treatment sessions, and they will be available for consultation, supporting participants as they, e.g., perform insertion exercises. To prevent a drop in adherence rates due to anticipatory anxiety during the course of treatment, exposure elements such as the insertion of one and two fingers are integrated into the intervention at an early stage. In a pilot trial evaluating an Internet-based intervention for women with vaginal penetration difficulties, the insertion exercises were introduced at the last stage of the intervention, and sessions including insertion exercises were associated with substantial non-adherence (67). The present study will evaluate the acceptability and efficacy of the newly developed intervention, providing valuable information on CBT treatment of GPPPD.

### Anticipated Results

We anticipate an increase in the ability to have sexual intercourse as well as positive cognitions toward vaginal penetration and intercourse in the IG compared to the WCG. A decrease is expected in genito-pelvic pain, fear of pain and penetration, and negative cognitions associated with intercourse and sexuality in the IG not in the WCG. With regard to potential pitfalls, recruiting the sample of women with GPPPD is a major challenge because the majority of them might not have contacted a health practitioner previously for their sexual dysfunction. Moreover, nonadherence to treatment is a common problem not only in Internet-based interventions but in psychotherapy in general. Especially in women with pain-penetration disorder, vaginal insertion is often associated with fear and avoidance behavior, increasing the likelihood for nonadherence to treatment despite the guidance included (67). As a troubleshooting strategy, we will include extensive adherence reminders *via* email and telephone in addition to guidance by an eCoach, which has been shown to be linked to higher treatment adherence in Internet-based interventions (106). The eCoach also closely monitors potential adverse effects in patients. If, contrary to expectations, participants experience a deterioration of symptoms or other adverse effects, the eCoach offers additional support and provides information on how to gain access to other treatment options. Additionally, participants can access information on further treatment options, e.g., face-to-face therapy, in module 8. Moreover, we assess potential negative effects with an evaluated questionnaire in a standardized procedure (97).

### Strengths

This study will contribute significantly to the literature and empirically tested treatments for GPPPD because, to the best of our knowledge, it is the first to investigate the efficacy of a guided Internet-based intervention for the treatment of GPPPD. A major strength of this study is its robust RCT design, commonly regarded as the gold standard for clinical trials. We will also include a high number of participants in this study to ensure sufficient power. In addition, missing data will be handled with MIs, and statistical analyses will be conducted with state-of-the-art methods. Another major advantage of this study is that it also includes a questionnaire on male sexual dysfunction, which the partners of participants will complete. The inclusion of this questionnaire will allow for an analysis of the influence of partners’ sexual disorders on participants’ treatment progress. Moreover, little is known about other moderators and mediators of the treatment outcome for GPPPD. In this study, potential moderators and mediators will be analyzed to understand for which women Internet-based interventions are likely to be the most effective and under what circumstances the intervention can be optimized for participants based on personal characteristics.

### Limitations

This study has the following limitations. First, the present study only includes women who have not been able to experience sexual intercourse for at least 6 months. Thus, our findings may not apply to women who are still able to have sexual intercourse but experience pain. Second, we will not include any objective measurement of GPPPD, e.g., gynecological examinations. Due to feasibility limitations, only self-reported measurements will be considered here. However, initial gynecological examinations are strongly recommended to make sure that the symptoms described by participants are not due to a medical condition. Future studies should focus on the development and evaluation of a diagnostic instrument for GPPPD which assesses all four dimensions in detail as well as distress associated with the condition.

## Conclusion

Overall, to complement research on GPPPD and to advance evidence-based treatment options, RCTs evaluating treatments for GPPPD are needed. Internet-based interventions might be a promising strategy to overcome some of the limitations of current treatment options including limited availability. This study will contribute to empirical research on GPPPD interventions and provide information about their acceptability and efficacy. It is, however, not yet clear which component of the multimodal cognitive-behavioral therapy is most important in treating GPPPD. If successful, this intervention could be made available to a large number of women because of the low threshold, lower costs and accessibility irrespective of place and time.

## Current Status

Recruitment began on April 1, 2016, and will continue approximately through December 31, 2017.

## Ethics Statement

This study has been approved by the ethics committee of the Friedrich-Alexander University Erlangen-Nürnberg (no. 324_15B).
